### Data collection

We will collect the clinical data from the laboratory results of all enrolled patients during admission and at outpatient clinic follow-up.

### Sample size

Sample size estimation is based on the null and alternative hypotheses. In our study, the null hypothesis is that “IVFe has no significantly different effect on Hb level and transfusion need after complex cardiac surgery” and we want to prove that the null hypothesis is wrong for replacing the alternative hypothesis by the two-sided test method. Previous reports [15, 16] suggested a 35% reduction in transfusion rate using IVFe but we set a higher transfusion rate (40%) considering the complexity and severity of cardiac surgery. The sample size calculation was based on superiority analysis under the hypothesis that all data was normally distributed data. We set the significance level at 0.05, the power at 80%, and the effect size was 0.5. A two-sided test was used and consequentially 97 patients were need for each group; however, we set each group as 107 considering a 10% dropout rate (total 214).

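### The 97 patients per group do not follow from the stated inputs (effect size 0.5 at 80% power needs 63 to 64), and the transfusion rates behind the calculation are left undefined

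*Protocol article*

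**What the plan says.** All of this stands in the Sample size section of the protocol article unless another section is named.

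- Error rates and effect: "We set the significance level at 0.05, the power at 80%, and the effect size was 0.5".
- Data model: a "superiority analysis under the hypothesis that all data was normally distributed data".
- Result: "A two-sided test was used and consequentially 97 patients were need for each group". This is then raised to 107 per group, 214 in total, for 10% dropout.
- Clinical rationale: earlier reports "suggested a 35% reduction in transfusion rate using IVFe but we set a higher transfusion rate (40"%), the reason given being how complex and severe the surgery is.

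Two other sections bear on this. Study objective and outcomes defines the primary endpoint both as the incidence of transfusion and as the mean number of units per patient. Statistical methods assigns the t test to continuous variables and the chi-square or Fisher's exact test to dichotomous ones.

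**The concern.** The 97 is presented as the consequence of the listed inputs, so a reader should be able to get from one to the other. An effect size of 0.5 under a normal model is most naturally a standardised mean difference, and that textbook case needs far fewer than 97 per group.

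The rationale is also about a different quantity. It speaks of a transfusion rate, which is binary, while the calculation assumes normal data. The two percentages are not enough to rebuild a binary calculation, because no control rate is paired with a treated rate.

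At stake is what the claimed 80% power refers to. If the trial ends without a significant difference, its readers need to know which effect it could have detected. The text as it stands does not let them work that out.

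**Working it through.** **Inputs.** Two-sided alpha 0.05, power 80%, effect size 0.5, normal data, and 97 per group (all from Sample size); 1:1 allocation (Randomization). Normal quantiles: 1.960 and 0.842, sum 2.802, squared 7.849.

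**Step 1: try to reproduce 97 from the stated inputs.** For two means with standardised difference d, n per group = 2 × 7.849 / d².

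- d = 0.5: 2 × 7.849 / 0.25 = 62.8, so 63. The t-test solution is 63.8, so 64.
- Reading 0.5 as Cohen's h (arcsine scale for proportions) uses the same formula and also gives 63.

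The stated figure is not reproduced.

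**Step 2: what 97 per group delivers on this scale.**

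- Power at d = 0.5: 0.5 × √(97/2) − 1.960 = 3.482 − 1.960 = 1.522, which is a power of 93.6%; the t test gives 93.4%.
- Effect detectable with 80% power: 2.802 × √(2/97) = 0.402; the t test gives 0.404.

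**Step 3: variants that might rescue 97.**

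- One-sided test, d = 0.5: 50.
- 90% power, two-sided: 85. 95% power: 104.
- Alpha 0.01, 80% power: 94.
- 0.5 as an odds ratio from 40% (40% to 25%): 152.
- 0.5 as a halving of 40% (40% to 20%): 82, or 91 with continuity correction.

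None gives 97.

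**Step 4: the transfusion rate.** For two proportions with mean p̄ (pooled variance under the null):

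n per group = [1.960 √(2p̄(1−p̄)) + 0.842 √(p₁(1−p₁) + p₂(1−p₂))]² / (p₁−p₂)²

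Power = Φ{ [|p₁−p₂| √n − 1.960 √(2p̄(1−p̄))] / √(p₁(1−p₁) + p₂(1−p₂)) }

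Worked case, 40% to 26% (p̄ = 0.33): n = (1.960 × 0.665 + 0.842 × 0.658)² / 0.14² = 3.448 / 0.0196 = 175.9, so 176. Power at n = 97: (0.14 × 9.849 − 1.303) / 0.658 = 0.115, which is 55%.

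The protocol gives no pair of rates, so each row below is an assumption about what was meant.

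| Reading of the text | Rates | n per group for 80% | Power at 97 per group |
|---|---|---|---|
| 40% is the control rate, 35% relative reduction | 40% to 26% | 176 | 55% |
| 40% is the control rate, 40% relative reduction | 40% to 24% | 133 | 67% |
| 40% is a relative reduction, control rate of 50% assumed | 50% to 30% | 93 | 82% |
| 40% is the treated rate after a 35% relative reduction | 61.5% to 40% | 84 | 86% |
| 0.5 is a relative reduction from 40% | 40% to 20% | 82 | 87% |
| 35 points absolute from 40% | 40% to 5% | 22 | over 99% |

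With Fisher's exact test, the first two rows fall to 49% and 62%. With all 107 per group evaluable, the pooled formula gives 59% and 71%. From a 40% control rate, 97 per group reaches 80% power only for a fall to about 21%, a relative reduction of roughly 46%.

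**The case against.** The best defence has three parts.

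First, 97 is more than 64, so for the only effect size the protocol labels, the trial has power to spare. That is correct, but it does not repair the statement: 97 is said to follow from 80% power and 0.5, and it does not.

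Second, the normal model need not be a mistake. Mean units transfused is part of the primary endpoint, and the null hypothesis in Sample size also names the Hb level. A standardised effect on a continuous measure is therefore a possible reading. This stands as far as it goes, and the fix should allow for it. On that reading, however, the required number is 64, so the mismatch remains.

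Third, the trial is not shown to be too small for transfusion incidence. A reader might infer that it lacks power for a reduction of 35 to 40% from a 40% transfusion rate. The protocol does not state that target. It gives 35% as a reduction from earlier reports and 40% as a higher rate. Because 40% is set against the 35% reduction, it could be the assumed reduction rather than the control rate. Several readings that the wording allows are adequately powered. This part of the defence stands in full, so any shortfall can be stated only conditionally.

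**Conclusion.** Wrong as written. The inputs in Sample size give 63 to 64 per group, not 97. At 97 per group, power for a standardised effect of 0.5 is about 93%, and 80% power corresponds to about 0.40. This rests only on the stated inputs and on reading 0.5 as a standardised effect; the other readings tried do not give 97 either.

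The section also leaves the transfusion calculation undefined. At 97 per group, power runs from 55% to over 99% across readings of the same sentence. The low figures, 55% and 67%, hold only if 40% is the control rate and the reduction is relative.

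Two further inferences are not supported:

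- **That 97 came from 60% versus 40%.** This pair does give 97 by the pooled formula, but the protocol states no 60% rate. Other pairs also give 97: 25% versus 10% without pooling gives 96.8.
- **That the dropout allowance is a material error.** 97 × 1.1 = 106.7 gives the stated 107, and 97 / 0.9 = 107.8 would give 108. One patient per group moves power by less than half a percentage point.

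**What to change.** Keep 214 patients and rewrite the Sample size paragraph around the calculation actually used:

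1. Name the endpoint it concerns: transfusion incidence or mean units transfused.
2. For incidence, state the assumed control rate, the assumed IVFe rate and the test. For mean units, state the assumed difference in means, the SD and the test.
3. Replace the effect size of 0.5 and the blanket normality assumption with those inputs. Say whether the 35% is relative or absolute and what the 40% denotes.
4. Restate the power that 97 per group gives under those inputs.
5. If a 40% control rate was intended, state the lower power for the cited reduction taken as relative: 55% for 40% to 26%. If a 40% relative reduction was the target, state 67% for 40% to 24%.

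The cost is a text correction, with no extra patients and no change to the analysis. Under item 5, the stated power becomes less favourable than 80%.

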### Statistical methods

Continuous variables were shown as means ± standard deviation (SD) and dichotomous variables are shown as numbers (percentages). Between-group comparisons of continuous variables were performed using the independent Student *t* test. Dichotomous variables were compared using the chi-square or Fisher’s exact tests, as appropriate. *P* values < 0.05 will be considered statistically significant.

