## Methods/design

### Study design

This prospective, double-blind, placebo-controlled, randomized, comparative, single-center trial was planned in Severance Cardiovascular Hospital, Seoul, Korea from August 2016 to August 2018 in patients undergoing re-do (re-do, second re-do, etc.) – or complicated valve replacement (double valve – aortic, mitral, with or without tricuspid surgery, CABG combined, arrhythmia surgery combined) cases. The trial protocol and related documents were approved by the competent authorities and Institutional Review Board (IRB) of the University of Yonsei (approval number: 4-2016-0502). The trial was conducted in accordance with Good Clinical Practice and the Declaration of Helsinki. Informed consent was obtained in writing prior to any trial-related activities. This trial was registered at ClinicalTrials (ClinicalTrials.gov, Identifier: NCT02862665) in August, 2016.

Patients will be randomly allocated to either the IV iron isomaltoside 1000 (IVFe) or the control (normal saline) group in a 1:1 ratio by means of computer-generated random numbers. IVFe administration is scheduled at 3 days before and after surgery. The patients will be checked by laboratory testing five times perioperatively at: (1) the preoperative baseline visit: reticulocyte count, Hb, plasma hepcidin, iron profiles (serum iron, serum ferritin, total iron-binding capacity, transferrin, transferrin saturation), coagulation profiles (PT, PTT), routine urinary analysis, and chemical profiles (aspartate aminotransferase (AST)/alanine aminotransaminase (ALT), serum creatinine, electrolytes, C-reactive protein (CRP), creatine kinase (CK), estimated glomerular filtration rate (GFR)), (2) start of therapy (first injection of IVFe 3 days before surgery): repeat laboratory test except for plasma hepcidin, (3) postoperative day 3 (just before the second injection of IVFe): repeat laboratory test except for urinary analysis, (4) postoperative day 10 or discharge day: repeat laboratory test except for plasma hepcidin and urinary analysis, and (5) postoperative week 4: repeat laboratory test except for plasma hepcidin and urinary analysis (Table 1).

**Table 1 Tab1:** Perioperative laboratory data sheet

	Lowest Hb/HCt	reticulocyte count	Highest PT (sec/INR)	Highest PTT	Highest GOT/GPT	Highest Cr	U/A RBC(±)	Serum iron	Transferrin sat (%)	Ferritin (ng/ml)	TIBC^a^	Hepcidin
Before surgery 2–3 days	/		/		/		(±)					
Just before surgery	/		/		/		(±)					
POD0	/		/		/		(±)					

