### Study objective and outcomes (primary and secondary outcomes)

The primary objective of the trial is to demonstrate that IVFe is superior compared to placebo in leading to less decrease in the Hb level and reducing the need of transfusion in patients undergoing complex cardiac surgery, which is a highly possible scenario for receiving a transfusion. The secondary objectives are to compare the effects of IVFe on the clinical (or surgical) outcomes (e.g., renal failure, respiratory failure, etc.) from reducing the need for blood transfusion and the stability of iron-related parameters. The final objective is to assess the role of the iron-regulatory protein, hepcidin, as a biomarker, as well as any association of hematological parameters with outcome. Thus, we decided the endpoints as followings: the primary endpoint is the comparison of perioperative transfusion requirements in terms of overall incidence and mean amounts of units of packed erythrocytes transfused per patient during and after the operation until discharge, and the secondary endpoint is the occurrence of postoperative major advanced complications (delayed ventilator therapy, AKI and all-cause mortality). A Hb concentration of less than 7 mg/dl during CPB, and less than 8 mg/dl after CPB and postoperatively, were used as transfusion thresholds. Intraoperatively, we measured the Hb concentration post induction and every 30 min during CPB, then at 10 min post CPB and post sternal closure, and postoperatively at the time of, and 8 h after, arrival at the ICU. After the day of surgery, we measured the Hb concentration in the morning if there was no excessive bleeding (over 1000 cm^3^) or symptoms of anemia. Any patients who have Hb concentrations higher than 8 mg/dl postoperatively, yet required transfusion due to symptoms of acute anemia, such as shortness of breath, change in respiratory rate and pulse rate, mental function deterioration, and myocardial ischemia, were excluded from the study. We also excluded patients who had undergone re-exploration for postoperative bleeding (postoperative bleeding was defined by total drainage volume (< 1000 cm^3^) during the 4 h after arrival in ICU).

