Postoperative variables included the amount of bleeding measured by chest-tube drainage after surgery, fluid input, urine output, and overall amount of ABT. Hb concentrations, PT, AST/ALT, and creatinine (Cr) levels were measured preoperatively, post anesthetic induction, and postoperative day (POD) 0 (day of the surgery after arrival in the ICU), 1, 2, 3, 4, and 7. Reticulocyte count and iron profiles were measured preoperatively and post anesthetic induction and at POD 3, and POD 10, and the changes in reticulocyte count from the baseline values were calculated. Postoperative variables also included the incidence of perioperative transfusion volume, the incidence of AKI within 48 h after surgery, new-onset AF after surgery, duration of ventilator care, ICU stay and hospital stay, and in-hospital mortality. Multiple ABT is defined as more than 1 unit of packed erythrocytes during the operation and until discharge. AKI is defined as elevation of serum Cr of ≥ 0.3 mg/dl or 50–200% from baseline using the modified Risk, Injury, Failure, Loss, and ESRD classification [14]. Surgical mortality is defined as all deaths that occur during the hospital stay or after hospital discharge but within 30 days postoperatively.

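### Only unadjusted tests are named although baseline haemoglobin is measured in every patient: a loss of precision of uncertain size, not a bias

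*Protocol article*

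**What the plan says.** All statements are in the protocol article.

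- **Statistical methods.** For binary outcomes, "Dichotomous variables were compared using the chi-square or" Fisher's exact test. For continuous outcomes, "Between-group comparisons of continuous variables were performed using the independent Student" t test. No model and no covariate is mentioned.
- **Study objective and outcomes.** The primary endpoint has two parts: "overall incidence and mean amounts of units of packed erythrocytes transfused per patient during and after the operation until discharge". Transfusion follows Hb thresholds, one during bypass and another afterwards: "less than 8 mg/dl after CPB and postoperatively, were used as transfusion thresholds". Patients transfused for symptoms while their postoperative Hb is above that level are removed from the study.
- **Study design.** The first of five laboratory time points is "the preoperative baseline visit: reticulocyte count, Hb, plasma hepcidin, iron profiles" and further tests. It is listed before the time point at which treatment starts.
- **Exclusion criteria and Intervention.** Entry sets a floor for Hb (9 g/dl in women, 10 g/dl in men) and no ceiling. Infusions are given whatever the Hb.
- **Randomization.** Allocation is 1:1 from computer-generated numbers. No stratification is described.
- **Reticulocytes.** After listing the sampling times, the outcomes section adds that "the changes in reticulocyte count from the baseline values were calculated".

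**The concern.** A patient is transfused when Hb falls below a set value, and the removal of symptom-driven transfusions ties the analysed endpoint more closely to that value. A patient who starts with a higher Hb has further to fall, so baseline Hb is the obvious prognostic covariate. It is recorded for everyone, may vary freely above the entry floor, and is not balanced by design. A crude test leaves the variation it explains in the error term. At stake is power for the primary endpoint and the width of every confidence interval, given up for no saving in data collection.

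**Working it through.** **1. The plan's own figure.** The Sample size section gives two-sided alpha 0.05, power 80%, effect size 0.5 and 97 per group. For a standardised mean difference of 0.5:

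n = 2 × (1.960 + 0.842)² / 0.5² = 2 × 7.85 / 0.25 ≈ 63 per group.

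So 97 does not follow from the stated effect size. A comparison of 60% with 40% does return 97:

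(1.960 × √0.50 + 0.842 × √0.48)² / 0.20² = 1.969² / 0.04 = 96.9.

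The article does not state that pair. This is a separate matter. It matters here only because the article supplies no usable pair of rates, so all rates below are assumptions.

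**2. Inputs for transfusion incidence.** n = 97 per group (Sample size). Three assumed rate pairs:
- 60% vs 40%: the pair that returns 97.
- 40% vs 26%: the section's 40% read as a control rate, with its 35% reduction applied, 40% × 0.65 = 26%.
- 40% vs 20%: a halving of 40%.

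The correlation ρ between baseline and nadir Hb is not given and is assumed from 0 to 0.7.

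**3. Simulation.** Nadir Hb = ρ × baseline + √(1 − ρ²) × noise, in standard units. A patient is transfused if the nadir falls below the cut that gives the assumed rate in that arm. There were 4,000 trials per cell. The uncorrected chi-square is set against the Wald test for arm in a logistic model with baseline Hb. Power, crude → adjusted:

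| ρ | 60% vs 40% | 40% vs 26% | 40% vs 20% |
|---|---|---|---|
| 0 | 79.2 → 78.9 | 53.8 → 53.3 | 87.8 → 87.3 |
| 0.2 | 80.8 → 80.7 | 56.4 → 56.8 | 86.8 → 87.0 |
| 0.3 | 79.4 → 81.3 | 55.4 → 57.0 | 87.4 → 88.2 |
| 0.5 | 80.6 → 86.2 | 54.2 → 61.2 | 87.0 → 91.2 |
| 0.7 | 82.1 → 93.2 | 55.0 → 70.3 | 86.8 → 95.6 |

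The gains are about 0 to 2 points at ρ ≤ 0.3, 4 to 7 at 0.5, and 9 to 15 at 0.7.

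**4. Second model as a check.** Here transfusion follows a logistic model with an assumed odds ratio per SD of baseline Hb (6,000 trials per cell). For 40% vs 26%, power goes from 56.3% to 56.6% at an odds ratio of 1.5, from 54.0% to 57.1% at 2, from 54.9% to 62.0% at 3, and from 55.1% to 66.8% at 4. The pattern is the same. With 40% in both arms, the adjusted test rejected in 4.7% to 4.9% of trials, so type I error is held.

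**5. Continuous outcomes.** Let r be the assumed correlation of an outcome with its own baseline, with equal variances at both times. Relative to the raw follow-up value (variance 1), ANCOVA has variance 1 − r² and a change score has 2(1 − r).

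| r | ANCOVA 1 − r² | Change score 2(1 − r) | Power from 80% with ANCOVA | 97 per group becomes |
|---|---|---|---|---|
| 0.3 | 0.91 | 1.40 | 83.6% | 89 |
| 0.5 | 0.75 | 1.00 | 89.9% | 73 |
| 0.7 | 0.51 | 0.60 | 97.5% | 50 |

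Power is Φ(2.802/√(1 − r²) − 1.960). The last column is 97 × (1 − r²), rounded up. Below r = 0.5 a change score is less precise than ignoring baseline, and ANCOVA is the most precise of the three in every row.

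**The case against.** The strongest reply is that the section is a four-sentence summary in a journal article and that covariate adjustment is usually settled in an analysis plan, which is not shown. An adjusted model may exist there. But the article is not silent: it assigns a test to each type of variable, and this point concerns that stated choice.

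Four stronger readings are tempting and are not supported.

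- **Bias.** A reader might infer that chance imbalance in Hb biases the crude comparison. It does not. Under randomisation the crude test's error rate already allows for such imbalance.
- **A large, established loss.** The trigger rule might suggest that baseline Hb all but determines transfusion. The documents do not show this. Surgical bleeding and dilution on bypass also drive nadir Hb, and the entry floor cuts off the lower tail. At weak correlations the gain disappears.
- **A contaminated baseline.** The article says "Reticulocyte count and iron profiles were measured preoperatively and post anesthetic induction", and the post-induction sample comes after the first infusion. A reader might infer that it serves as baseline. Nothing in the article uses it so, and Study design names an earlier visit as baseline.
- **Change scores throughout.** They are stated for the reticulocyte count only, with no test attached to them.

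It is also fair to say that a remedy confined to incidence would miss half the primary endpoint, which includes mean units.

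**Conclusion.** The point holds as one of efficiency. The article names only unadjusted tests while an already collected, plausibly prognostic covariate goes unused. For transfusion incidence at 97 per group, the gain from adjustment runs from about zero to about 15 power points. Where it falls depends on a correlation that the documents do not give and on assumed rates. The gain is material from a correlation of about 0.5 and negligible at 0.3 or less. The simulated gain is for the arm coefficient in the logistic model, with baseline Hb as the only covariate. No gain has been calculated for mean units. A crude analysis would still be valid, so the change is worth making but the trial's conclusions do not depend on it.

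**What to change.** Specify the following before unblinding. The article reports recruitment as incomplete at submission.

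1. **Transfusion incidence:** logistic regression on arm and continuous baseline Hb, reported as a standardised risk difference with a 95% confidence interval. Standardising keeps the effect on the marginal risk scale in place of a conditional odds ratio. Keep the crude chi-square as a sensitivity analysis.
2. **Mean units transfused:** adjust for baseline Hb too, for example by linear regression on arm and baseline Hb with robust standard errors, which still estimates a difference in means.
3. **Hb, reticulocytes and iron parameters:** ANCOVA on the baseline value of the same variable, in place of a crude t test or change score.
4. **Baseline:** state that it is the preoperative baseline visit in Study design, sampled before the first infusion.

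The cost is one model degree of freedom and a documented change to the analysis wording. No new data are needed. If baseline Hb proves uninformative, the simulated loss is half a power point or less (the ρ = 0 row).

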## Discussion

ABT is a recognized risk factor for morbidity and mortality after cardiac surgery [6, 17]. Despite efforts to reduce ABT, it remains common in cardiac surgery. Several studies have been published about the effect of erythropoietic agents such as Recombinant Human Erythropoietin (rHuEPO) [18–20] and IV iron isomaltoside 1000 (Monofer®) [21, 22]. For rHuEPO, the theoretical basis for selecting the timing of rHuEPO administration was based on the assumption that a pre-emptive single dose of rHuEPO may mitigate the inflammatory response-induced blunting of erythropoiesis; however, this hypothesis remains speculative unless we also evaluate the representative inflammatory markers. Also, the potential risk of rHuEPO has always been considered a considerable burden including the possible complications of rHuEPO which include hypertension, headache, tachycardia, nausea, vomiting, hypercalcemia, diarrhea, and thromboembolic complications. Recently, therefore, direct IV iron replacement agents have received attention as alternatives to rHuEPO therapy for reducing transfusion need. In various surgical fields, the effect of IV iron replacement therapy on clinical outcomes by reducing ABT have been analyzed and they showed favorable results compared with simple iron-replacement therapy per os. In the study by Muñoz et al., ABT, postoperative nosocomial infection, 30-day mortality, and length of hospital stay (LHS) from 2547 patients undergoing elective lower-limb arthroplasty (*n* = 1186) or hip fracture repair (*n* = 1361) were compared between patients who received either very-short-term perioperative IV iron (200–600 mg; *n* = 1538), with or without rHuEPO (40,000 IU), or standard treatment (*n* = 1009). They suggested that very-short-term perioperative administration of IV iron, with or without rHuEPO, in major lower-limb orthopedic procedures are associated with reduced ABT rates and LHS, without increasing postoperative morbidity or mortality [16].

Froessler et al. also analyzed whether perioperative IV iron reduced the need for ABT in abdominal surgery patients. Seventy-two patients with iron-deficiency anemia were assigned to the study which suggested that the administration of perioperative IV iron reduces the need for ABT, and is associated with a shorter LHS, enhanced restoration of iron stores, and a higher mean Hb concentration 4 weeks after surgery [15].

Focusing on the cardiac surgery itself, Johansson et al. explored whether IV iron isomaltoside 1000 (Monofer®) results in a better regeneration of Hb levels and prevented anemia compared to placebo in preoperative non-anemic patients undergoing cardiac surgery. They showed that a single, perioperative 1000-mg dose of IV iron isomaltoside 1000 significantly increased the Hb level and prevented anemia 4 weeks after surgery, with a short-term safety profile similar to placebo [21]. However, this trial was an exploratory trial with only a small sample size of 60 patients and relatively simple cardiac surgery such as CABG. So, the actual risk of bleeding is too low to perform transfusion compared with our protocol. Our protocol includes patients undergoing complicated valve surgery, such as re-operation from previous valve failure, combined with CABG, arrhythmia surgery, etc.; therefore, it is more easily reproducible to compare ABT rate between groups in the “real” surgical world. Also, our protocol contains an analysis of hepcidin effect in which it is unclear how hepcidin affects the IVFe as it works to increase the Hb and improve clinical outcomes.

